#### 3.3.1 Secondary Objectives

- To measure the proportion of children managed in each study arm who do not respond to treatment (treatment failures).
- To measure the cost-effectiveness of having CHWs manage malaria using Coartem® with RDTs compared to without the use of RDTs.
- To measure the proportion of acute febrile illnesses in children which are RDT-positive
- To determine the burden of non-malaria febrile illness among a rural population of children reporting fever

**3.3.2 Secondary Hypotheses**

- The use of RDTs in the management of febrile illness coupled with pneumonia treatment at the community level instead of referring will reduce the rate of treatment failure.
- The use of Coartem® by CHWs will be more cost effective when guided by RDTs than when guided by clinical criteria alone.
- The use of RDTs will demonstrate that a significant proportion of children presenting with acute febrile illness and who would otherwise be treated for malaria do not in fact have malaria.

**3.5 Secondary Outcomes**

- Proportion of children treated who do not respond to treatment (experience treatment failure – defined here as any of the following:
  - Failure to clear symptoms by day 5 after treatment.
  - Subsequent referral to health center or hospital despite treatment.
  - Development of severe signs despite treatment
  - Use of additional antibiotics or antimalarials beyond those prescribed and dispensed by the CHW.
  - Serious adverse event considered possibly or probably related to drugs.
- Costs of treatment and cost associated with the use of RDTs by CHWs
  - Initial and ongoing training costs per CHW
  - Costs of RDT kits/reagents
  - Costs per course of Coartem®
  - Other costs associated with the use of RDTs by CHWs
  - Cost associated with referral
- Proportion of febrile children with a positive RDT result

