# 4.2 Study design

The study will be a cluster-randomized controlled trial. A study cluster will be defined as the catchment area of a community health post. CHWs work from a community health post with well defined catchment area and population within a health facility catchment area and are supervised by the staff of the health facility. The clusters (community health post catchment area) will be matched in pairs according to the health facility catchment area they belong to, the distance from the health facility and the population size. Randomization will then be done from among the matched clusters to select the intervention and the control arms. CHWs in both the intervention and control arms will receive training in the assessment and classification of children presenting with fever and/or cough/difficult breathing. The CHWs in the intervention arm will be supplied with RDTs, Coartem® and amoxicillin. The intervention CHWs will be trained to use RDTs in patients with reported fever and provide those with a positive result with Coartem while patients suspected of pneumonia (based on fast breathing) will be treated with amoxicillin as per the standard of care at health facilities and monitored. Those with negative RDT result will be treated with antipyretic and asked to return if they do not get better after 48 hours or condition deteriorates. In the control group, no RDT will be performed. The CHWs will be supplied with Coartem to treat malaria/febrile illness as per the IMCI guidelines and patients suspected of pneumonia will be referred to the health facility for treatment as per the current practice. The supply of the drugs and RDTs will come through the normal MOH sources. The study will utilize specialized field workers (data collectors and data supervisors) to visit CHWs to collect data on their consultations and follow-up children treated by CHWs. Consent will be sought from caregivers to allow us collect data by which to assess the effectiveness of the intervention. Caregivers in both the intervention and control arms are not obliged to receive care from the CHWs. They are free to go to any of the health facilities in the study area instead of a CHW. The study will collaborate with the MOH and the DHMTs to ensure that the health facilities in the study area have RDTs, Coartem and amoxicillin.

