### 4.5. Roles and responsibilities of community health workers

The primary role of the CHWs is to serve as the households’ first point of contact with the health system. They will classify the child’s illness and provide specific drug treatment.

The key responsibilities will include:

- taking a history from the caretaker
- assessing the child including respiratory rate, temperature and the presence of danger signs;
- treating or referring as appropriate
- dispensing specific medication and observing the child taking the first dose
- providing the caretaker with instructions for the remainder of the treatment course, as well as for care of the sick child in the home.
- counseling caregivers to return if condition deteriorates or experience any adverse effects
- conveying a sense of urgency to the caretaker when a referral is indicated, administering start dose of medication if indicated, and providing a referral slip.
- managing a stock of medications and supplies
- maintaining simple records and registers
- conducting community education

In the intervention arm, the CHWs will also perform and interpret RDTs

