#### 4.14 Follow-up

The patients seen by the CHWs with fever and/or fast breathing will be followed up at home by the data collectors to assess the outcome of the treatment given or recommended. The follow-up visit will occur 5-7 days after the visit to the CHW. The data collectors will make contacts with CHWs at least every other day to take particulars of children treated from the identification and baseline forms in order to schedule a follow-up visit. During the follow-up visits, the data collectors will interview the caregiver (the person who took the child to see the CHW or in his/her absence a family member who knows sufficiently about the illness and the care received); and perform some basic examination including taking of temperature and counting of respiratory rate. Information that will be collected during the follow-up visits will include, complaints that prompted heath seeking at the CHW, treatment given, counseling or advice given, referrals, self-reported adherence to the medication, outcome of the visitation, alternative treatment after the visit and where such alternative treatment was obtained and current general condition and complaints. They will also be asked questions to explain inappropriate treatment. If a subject is found not to be improving, the data collector will advise the caregiver to go to the clinic.

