#### Routine data collected from CHWs and facility-based records.

#### Performance assessments of CHW skills.

#### Follow-up visits of children treated by CHWs at home.

#### A set of household surveys.

CHWs will keep an outpatient department (OPD) register in which each person attended to will be registered. The OPD register will provide information on the name of the patient, address, sex, age or date of birth, date of onset of illness, main complaints, classification of the disease, drugs given, and comments (recovered, referred or died). The CHW will then make a monthly summary of the register. In addition, the CHW will keep a daily tally sheet for drugs and supplies dispensed and make a monthly summary. The CHW will keep a record of referred cases. The record (which is supplemented by information received from the health center) will include date and time of referral, presenting signs and symptoms (diagnosis), date and time seen at referred centre, date of discharge, and final diagnosis. The CHW will also complete an “identification and baseline form” for every child between six months and five years with fever or fast breathing. The health facilities in the area will keep morbidity and mortality records including information on all CHW referrals.

On a monthly basis the data collectors will visit the CHW and health facility and collect summaries of records kept in special design case report forms (CRFs). The information collected on CRFs for CHWs will include number of children seen, those classified as malaria or pneumonia or both, RDTs performed, drugs dispensed, referrals and whether a supervisory visit was made The information that will be collected on CRF at the health facility will include number of malaria and pneumonia cases, severe malaria and pneumonia cases, referrals from CHWs, deaths by cause, availability of RDTs, Coartem**®** and amoxicillin.

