The data collectors will visit the CHWs at least every other day to collect completed identification and baseline forms to schedule a follow-up visit. The DC will check with the CHW register to ensure that every child seen by the CHW with fever of fast breathing has a completed identification and baseline form. The follow-up visits will be made at 5-7 days after the caregiver visits the CHW. Information that will be collected during the Day 5 – 7 follow-up visits will include, complaints that prompted heath seeking at the CHW, whether rapid diagnostic test was done, treatment given, counseling or advice given, self-reported adherence to the medication, outcome of the visitation, alternative treatment after the visit and where such alternative treatment was obtained, current general condition and complaints and results of temperature and respiratory rate taken.

Economic cost data from health facilities will be collected by the data collectors. These data will include the average costs associated with treating uncomplicated and severe cases of malaria and pneumonia, including overhead, equipment, personnel, medicines, and supplies. This information will then be matched with the case records in order to estimate the facility-based costs of treatment for children in intervention and control groups.

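### The symptom component of treatment failure is defined at day 5 after treatment, but the only scheduled observation is current status 5 to 7 days after the CHW contact, so it cannot be scored as defined

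*Protocol*

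**What the plan says.** Section 3.5 defines treatment failure as any one of five components. The first is "Failure to clear symptoms by day 5 after treatment". The other four are events: later referral, severe signs, additional antibiotics or antimalarials, and a drug-related serious adverse event.

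Section 4.14 sets the assessment: "The follow-up visit will occur 5-7 days after the visit to the CHW". Section 5.1 repeats the timing: "The follow-up visits will be made at 5-7 days after the caregiver visits the CHW". For the state of the child, Section 5.1 lists "current general condition and complaints and results of temperature and respiratory rate taken". The interview also covers "outcome of the visitation, alternative treatment after the visit and where such alternative treatment was obtained", without saying what the first of these items means or tying it to a day. The CHW's register has a comment field for recovery, referral or death, again with no scheduled day.

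The start of pneumonia treatment differs by arm. In the intervention arm the CHW gives amoxicillin at the contact, and the CHW's duties in Section 4.5 include "dispensing specific medication and observing the child taking the first dose". In the control arm, under Section 4.2, "patients suspected of pneumonia will be referred to the health facility for treatment as per the current practice".

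Section 3.3.2 states a between-arm hypothesis on treatment failure, and Section 4.18 makes treatment failure the health outcome of the economic analysis.

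**The concern.** The definition asks about a fixed day counted from treatment. The visit gives a snapshot on one of three days counted from the CHW contact. If no clearance date is taken, the snapshot cannot be converted into the defined status, and no later analysis plan can recover a date that was never collected.

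Two groups of children are affected. Those whose symptoms clear on day 6 or 7 are scored by the day the data collector happened to come. Referred children who start treatment at the facility some time after the contact may be visited before day 5 of their treatment.

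At stake is the level of a secondary outcome that carries a stated hypothesis and supplies the outcome term in the cost-effectiveness ratio of Section 6.3.

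**Working it through.** The protocol states no rate, power or sample size for treatment failure, so there is no figure of its own to reproduce. The check compares the definition with the visit schedule and then illustrates the size. I read the definition's day count as running from the start of treatment, which Section 3.5 does not say outright.

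**1. Definition against observation**

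| | Section 3.5 | Sections 4.14 and 5.1 |
|---|---|---|
| Day zero | Treatment | CHW contact |
| Time point | Day 5 | Day 5, 6 or 7 |
| Information | Whether symptoms had cleared by then | State of the child at the visit |

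**2. Child treated at the contact.** A day-5 visit gives the defined status. At a day-6 or day-7 visit, a child still symptomatic has failed (leaving relapse aside). A child who is well cannot be classified, because clearance may have come on day 5 or earlier (success) or later (failure). Late visits therefore undercount failures.

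**3. Child treated at the facility after referral.** Let d be the visit day after contact and k the delay in days from contact to treatment. Time on treatment at the visit is d − k. The protocol gives no k (referral compliance within 24 hours is itself an outcome in Section 3.6), so 0, 1 and 2 days are assumed.

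| Visit day d | k = 0 | k = 1 | k = 2 |
|---|---|---|---|
| 5 | 5 | 4 | 3 |
| 6 | 6 | 5 | 4 |
| 7 | 7 | 6 | 5 |

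Wherever the entry is below 5, the defined status has not yet occurred at the visit. That is so for a day-5 visit with either delay and for a day-6 visit with a two-day delay. A day-7 visit reaches day 5 of treatment for delays of up to two days.

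**4. Size of the visit-day effect (assumed rates, not trial data).** Let s be the share still symptomatic on day 5 and h the share of those clearing per day. The component as scored on day d is s × (1 − h)^(d − 5).

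| s | h | Day 5 | Day 6 | Day 7 | Fall, day 5 to 7 |
|---|---|---|---|---|---|
| 10% | 20% | 10.0% | 8.0% | 0.10 × 0.8² = 6.4% | 3.6 points |
| 20% | 30% | 20.0% | 14.0% | 0.20 × 0.7² = 9.8% | 10.2 points |
| 30% | 30% | 30.0% | 21.0% | 0.30 × 0.7² = 14.7% | 15.3 points |

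A constant-hazard version agrees. With s = 20% and a hazard of 0.35 per day, the scores are 20.0%, 14.1% and 9.9% on days 5, 6 and 7. The day-7 score runs from 13.4% to 7.4% as the hazard goes from 0.2 to 0.5.

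The right-hand column is an extreme, since it moves every child from day 5 to day 7. With visits spread evenly over the three days, the constant-hazard version gives (20.0 + 14.1 + 9.9)/3 = 14.7%, which is 5.3 points below the day-5 value.

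**5. Between arms.** If both arms have the same true curve, the same treatment start and the same mix of visit days, the formula returns the same score in each. Variation in visit day that the arms share changes the level and creates no false difference.

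**The case against.** Several points on the other side have force.

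*The lists are open.* The visit items are introduced as what will be included, and the forms are still to be developed and piloted (Sections 4.9 and 5.3), so a form could add a clearance date. That is possible, but the protocol does not provide for it, and the definition depends on it.

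*There are other records.* The visit interview takes an undefined outcome item, the register has its comment field, and the returned referral form dates facility attendance (Section 4.12). The visit is therefore not the only observation of any kind. It is the only scheduled symptom assessment, and none of the other records gives a day-5 status.

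*The clock problem is narrow.* By the plan's figures, fever cases are 1518 of 2042 children (524 + 1518). Children given Coartem by the CHW start at the contact in either arm. A start dose may be given on referral if indicated (Section 4.12), although Section 4.2 names only Coartem as supplied to control CHWs. This stands as a limit on size.

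*Only one component is hit directly.* The other four are events, so a shift in this component need not carry one-for-one into the composite. This also stands.

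*Referral delay is not bias.* A reader might infer that later facility treatment artificially inflates control failures. The documents do not support that. Section 3.3.2 compares community treatment with referral, and Section 6.1 specifies intent-to-treat, so delay caused by referral belongs to the strategy being compared.

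*No imbalance in visit days is shown.* A reader might also infer a false difference between arms from data-collector scheduling. Both arms share one schedule, and clusters are matched on facility catchment, distance and population (Section 4.2). The protocol is silent on whether data collectors know the arm, so differential scheduling cannot be asserted.

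**Conclusion.** The mismatch stands. As written, the symptom component cannot be scored from the data the protocol says will be collected. Its value depends on visit day for children who clear on day 6 or 7, and it may be undefined at the visit for referred control pneumonia cases treated late.

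The consequence is mainly a misstated level of failure, in one of five components of a secondary outcome. The range of about 4 to 15 points is illustrative. It rests on 10 to 30% of children being symptomatic on day 5, 20 to 30% of those clearing per day, and every visit moving from day 5 to day 7. The effect on the composite cannot be stated from the documents, and no between-arm bias is established.

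It still merits correction before the forms are final, because the outcome carries a hypothesis and feeds the economic analysis.

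**What to change.** - In Section 3.5, define the component as symptoms still present on day 5 after the first CHW contact, in both arms. Every scheduled visit then reaches the defined day, and referral delay counts as part of the strategy compared.
- On the follow-up form, ask for the date each presenting symptom cleared, and score the component from that date.
- Record the visit date and report visit day by arm, so that any imbalance can be seen.

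The cost is one line in Section 3.5, a few form items and up to two days of caregiver recall (a day-7 visit asking about day 5). Measured temperature and respiratory rate would remain findings of the visit day. The 5-to-7-day window can stay. Narrowing it to a single day would cost follow-up in an area with poor roads and seasonally cut-off villages (Section 4.1), and is not needed once the clearance date is recorded.

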**4.11.1 Rationale for choosing Amoxicillin**

The decision to use amoxicillin was made in conjunction with the IMCI unit of the Zambian MOH. We chose amoxicillin based on the comparative therapeutic advantages and disadvantages of several candidate antibiotics, local patterns of use, and restrictions on the categories of antibiotics that can be used in community settings according to current Zambian health policies. It is one of the drugs recommended by the Zambia National treatment guidelines for pneumonia. Amoxicillin has a long safety record, is readily available in Zambia, is inexpensive, widely accepted by patients and clinicians, and has excellent bioavailability when taken orally.

The very few serious side effects to amoxicillin that occur are due to hypersensitivity. Since it will be given in an oral form, this form of reaction is not anticipated. Less acute reactions, respiratory and skin manifestation including tightness in the chest, itching and urticaria rash may occur and we will look out for them.

We are considering the use of tablets over syrups as tablets offer advantages over the syrup, which include lower cost, easier dosing, easier ability to comply, and ease of packaging and distribution.

Treatment Chart

| Weight | Age | Dose | Total dose |
| --- | --- | --- | --- |
| 4-9 kg | 6-11 months | ½ tab 3x/day  5ml (1tsp) 3x/day | 4½ tabs  45 ml |
| 10-19 kg | 12 m – 5yrs | 1 tab 3x/day  10ml 3x/day | 9 tabs  90 ml |

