#### 4.18 Economic Analyses

The overall goal of the economic evaluation is to determine the cost effectiveness and the difference in economic costs between the use of RDTs in the diagnosis and treatment of malaria (the intervention) and the presumptive treatment of fever with Coartem (the control). The economic analysis will also determine the incremental cost-effectiveness of the use of RDTs in the diagnosis and treatment of malaria so as to provide an additional measure by which to judge the usefulness of the ZIMMAPS intervention. The economic analyses will be based both on cross sectional data collected from health facilities and data collected longitudinally from the caretakers of ill children. The key indicators will be direct economic costs incurred in both the treatment and control areas. We will measure such costs at the household, health care provider, and medical facility levels related to diagnosis and treatment of malaria and pneumonia by CHWs, including referrals. Health outcome will be measured as treatment failure defined earlier.

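### The treatment-failure definition counts a control child with fast breathing as a failure for receiving the facility antibiotic that the design refers the child to get

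*Protocol*

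**What the plan says.** Section 3.5 lists treatment failure as a secondary outcome: "experience treatment failure – defined here as any of the following". Five components follow. Two matter here: "Use of additional antibiotics or antimalarials beyond those prescribed and dispensed by the CHW" and "Subsequent referral to health center or hospital despite treatment".

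Section 4.2 gives the arms different pathways for fast breathing. On the intervention side, "The CHWs in the intervention arm will be supplied with RDTs, Coartem® and amoxicillin". On the control side, CHWs hold Coartem, and "patients suspected of pneumonia will be referred to the health facility for treatment as per the current practice".

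Section 3.3.2 hypothesises that RDT use "coupled with pneumonia treatment at the community level instead of referring will reduce the rate of treatment failure". Section 6.2 analyses this outcome in the same way as the primary outcomes. Section 4.18 carries it into the economic evaluation: "Health outcome will be measured as treatment failure defined earlier". It then forms the denominator, OA − OB, of the ratio in section 6.3. None of sections 3.5, 4.18 or 6.1 to 6.3 exempts drugs given at the referral that the design requires.

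**The concern.** The antibiotic component is anchored to what the CHW dispensed, yet by design only one arm's CHWs dispense an antibiotic. The source of the first course, rather than the child's response to it, then decides whether the child has failed.

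Two consequences show that the component does not measure non-response:

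- A referred control child who gets prompt, correctly dosed amoxicillin at the facility can be a success on the first primary outcome (section 3.4) and a failure on the first secondary outcome.
- Better referral compliance, which section 3.6 tracks, raises the control arm's failure rate.

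Among fast-breathing children, the hypothesis of fewer failures could be met with no clinical difference. The economic analysis in section 4.18 is framed as RDT-guided against presumptive malaria treatment, so an artefact of pneumonia referral would be attributed to RDTs.

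**Working it through.** **The plan's own figures.** The protocol gives no expected rate, sample size or power for treatment failure, so there is nothing to reproduce for that outcome. The two sample totals used as weights below do reproduce: 456 × 1.15 = 524.4 (stated 524) and 1320 × 1.15 = 1518 (stated 1518).

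**Inputs**
- f, true failure rate, set equal in both arms: 10%, range 5–30% (assumption).
- c, share of control fast-breathing children who receive the facility antibiotic: 50%, from the section 4.3 estimate of early and appropriate treatment, used as a proxy; range 25–100% (assumption).
- s, share of fast-breathing children among all those followed. From the section 4.1 incidence figures (pneumonia 70–80 and malaria 900–1200 per 1000 under-fives): 70/(70 + 1200) = 5.5% to 80/(80 + 900) = 8.2%. From the sample-size targets, ignoring overlap: 524/(524 + 1518) = 25.7%.

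**Fast-breathing children.** Counted control failure is f + (1 − f)c, against f in the intervention arm. The spurious difference is (1 − f)c, because children who would fail anyway are not counted twice.

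| f | c = 25% | c = 50% | c = 100% |
|---|---|---|---|
| 5% | 23.75 | 47.5 | 95 |
| 10% | 22.5 | 45 | 90 |
| 30% | 17.5 | 35 | 70 |

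(percentage points)

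At f = 10% and c = 50%, counted failure is 0.10 + 0.90 × 0.50 = 55% in control against 10%.

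**Chance of a false positive in fast-breathing children.** Take 19 clusters of 12 per arm (228 children) at intracluster correlation 0.25, the plan's largest value. The design effect is 1 + 11 × 0.25 = 3.75 and the effective size is 228/3.75 = 60.8 per arm. With f = 10% in both arms, a two-sided 5% test favours the intervention with probability about 87% at c = 25% (32.5% against 10%), and above 99% at c = 50%.

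**Pooled rate, before any offset.** The artefact is s(1 − f)c. At f = 10% and c = 50%:
- s = 5.5%: 0.055 × 0.45 = 2.5 points
- s = 8.2%: 0.082 × 0.45 = 3.7 points
- s = 25.7%: 0.257 × 0.45 = 11.5 points

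**Offset in the other direction.** The same component counts antimalarials. RDT-negative intervention children get no Coartem from the CHW, so one who obtains an antimalarial elsewhere is a failure; section 3.6 plans to measure this. Febrile control children already had Coartem from the CHW. The offset is (febrile share) × (RDT-negative share) × (share obtaining an antimalarial) × (1 − f). The share obtaining one is an assumption throughout.
- Febrile share about 93%, 20% negative (the section 4.3 hypothesis), 10% obtaining: 0.93 × 0.20 × 0.10 × 0.90 = 1.7 points.
- As above with 50% negative (assumption): 4.2 points.
- Sample-size weights, febrile share 74.3%: 3.3 points at 50% negative and 10% obtaining; 16 points at 80% and 30%.

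Set against 2.5–3.7 or 11.5 points, the net can take either sign.

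**The case against.** **Reach.** Only a secondary outcome and the cost-effectiveness ratio are touched, and the section 3.3.2 hypothesis covers RDT use and pneumonia treatment together, so the pooled rate is the natural test. There the artefact may be small and may be offset. This stands: a one-way bias in the pooled result is not established. The ratio of sample-size targets is also a weak guide to case mix, because the targets were set separately and section 4.14 follows every child with fever or fast breathing. The incidence-based share has its own weakness, since CHW-counted fast breathing may exceed recorded pneumonia.

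**Denominator.** Section 3.5 speaks of children treated, section 3.3.1 of children managed in each arm. On the narrower wording, a control child with fast breathing and no fever receives no CHW drug and may drop out. That limits the artefact to children with both signs but does not remove it. It would also exclude control children whose intervention counterparts stay in.

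**Stronger readings that a reader might infer.** One is that the required referral is itself a failure. The wording is "Subsequent referral to health center or hospital despite treatment", and a first-contact referral need be neither subsequent nor despite treatment. The case of a febrile control child given Coartem and referred at the same visit is merely unclear. Another is that the first primary outcome is similarly skewed because it names only amoxicillin. Section 4.11.1 does say "It is one of the drugs recommended by the Zambia National treatment guidelines for pneumonia", but section 4.2 presents amoxicillin as the facility standard and commits the study to working with the health authorities to keep it in stock. Nothing shows that facilities would use another drug.

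**Conclusion.** The antibiotic component is wrong as written and, because any one component suffices, it is enough alone to misclassify control children treated as planned. In fast-breathing children the direction is certain and the size is (1 − f)c: 45 points at f = 10% and c = 50%, and 17.5 to 95 points over the ranges shown. In the pooled rate the gross artefact is about 2.5 to 4 points on incidence-based shares, or about 11.5 on the sample-size ratio, and its net direction is not certain. The pooled sizes rest on an assumed true failure rate, on the section 4.3 figure standing in for antibiotic receipt, and on an uncertain case mix. The cost-effectiveness ratio inherits the problem through OA − OB. The primary outcomes and the sample size are not affected.

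**What to change.** In section 3.5, state that a referral made at the first CHW consultation under the arm's own algorithm, and the first drug course prescribed at that referral visit, are part of assigned management and are not failures.

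In both arms, count as failure any later change or addition of antibiotic or antimalarial, any later referral, severe signs, persistent symptoms, or a drug-related serious adverse event. Time these from the index CHW consultation, whether or not the family complied with referral. A clock starting only after a completed first course would miss drug switches during the 5-day course of section 3.4, given follow-up at day 5–7. It would also exempt control children who never reached the facility.

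Use one denominator, all children managed in each arm, reconciling sections 3.3.1 and 3.5. Report each component by arm and by fast-breathing status, and use this definition in the cost-effectiveness ratio. With equal true rates of 10%, fast-breathing children then score 10% in both arms. Antimalarials obtained elsewhere by RDT-negative children would still count, so reporting by component remains necessary.

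The data are already planned: the referral form (section 4.12) records facility treatment and dates, and the day 5–7 interview (sections 4.14 and 5.1) records alternative treatment and its source. The cost is slightly more outcome coding and a smaller expected difference between arms.
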